## Abstract

**Background:**

Around 80% of intrauterine growth restricted (IUGR) infants are born at term. They have an increase in perinatal mortality and morbidity including behavioral problems, minor developmental delay and spastic cerebral palsy. Management is controversial, in particular the decision whether to induce labour or await spontaneous delivery with strict fetal and maternal surveillance. We propose a randomised trial to compare effectiveness, costs and maternal quality of life for induction of labour versus expectant management in women with a suspected IUGR fetus at term.

**Methods/design:**

The proposed trial is a multi-centre randomised study in pregnant women who are suspected on clinical grounds of having an IUGR child at a gestational age between 36+0 and 41+0 weeks. After informed consent women will be randomly allocated to either induction of labour or expectant management with maternal and fetal monitoring. Randomisation will be web-based. The primary outcome measure will be a composite neonatal morbidity and mortality. Secondary outcomes will be severe maternal morbidity, maternal quality of life and costs. Moreover, we aim to assess neurodevelopmental and neurobehavioral outcome at two years as assessed by a postal enquiry (Child Behavioral Check List-CBCL and Ages and Stages Questionnaire-ASQ). Analysis will be by intention to treat. Quality of life analysis and a preference study will also be performed in the same study population. Health technology assessment with an economic analysis is part of this so called Digitat trial (Disproportionate Intrauterine Growth Intervention Trial At Term). The study aims to include 325 patients per arm.

**Discussion:**

This trial will provide evidence for which strategy is superior in terms of neonatal and maternal morbidity and mortality, costs and maternal quality of life aspects. This will be the first randomised trial for IUGR at term.

**Trial registration:**

Dutch Trial Register and ISRCTN-Register: ISRCTN10363217.

## Background

Around 80% of intrauterine growth restricted (IUGR) infants are born at term [1]. When pregnancy is complicated by IUGR, there is, whether term or preterm, a clear association with an increase in neonatal mortality and neonatal morbidity (short and long term) [2-4]. The long term morbidity ranges from behavioral problems and minor developmental delay to spastic cerebral palsy [5-10]. However, not all studies, especially after excluding congenital anomalies, confirm these findings [11]. Besides fetal asphyxia, meconium aspiration, fetal heart rate abnormalities and low Apgar score, also more admittances to and longer stays at neonatal intensive care units are reported. This might partly be related to a higher prevalence of hypoglycaemia, neonatal sepsis, hypothermia and haematological problems as thrombocytopenia and polycythemia in these neonates [12-14].

When a fetus is small for gestational age (SGA), defined on the basis of a birth weight below the 10^th ^centile, there is the concern that the fetus might be afflicted by IUGR [15]. As SGA is defined on the basis of an arbitrary chosen cutoff birth weight centile, not all infants falling below the 10^th ^centile are abnormally small because of growth restriction. Many neonates with a birth weight below the 10^th ^centile are representing the normal spectrum of fetal growth [11]. Variation in birth weight is related to many factors as maternal height, weight, parity and fetal gender, but also ethnicity [16]. For that reason optimal growth for any fetus should be related to the fetus' own individual optimal growth curve [17-19]. Intrauterine growth restriction has to be defined on further knowledge such as Doppler abnormalities as seen in placental perfusion, eventually in combination with abnormalities in cerebral perfusion [20,21] and possibly also by neonatal measurements as the Ponderal Index [22,23].

A reduction of fetal growth is exponentially associated with a higher perinatal mortality [24] and morbidity [25,26]. Doppler umbilical artery studies have shown that absence of end diastolic velocities, indicative of IUGR based on severe placental insufficiency is associated with a higher rate of caesarean deliveries and an increased incidence of perinatal and neonatal mortality [27-30]. However, a normal umbilical artery Doppler study at term gestation might be falsely reassuring, while a normal cerebral artery study might identify the fetus not likely having a major adverse outcome [31].

Most of the growth restricted children experience an accelerated growth, especially of the head circumference, during the first 6 months after birth [32]. However, this upward centile crossing or 'catch up growth' is not complete, even at the age of seven years [33]. Moreover head circumference seems to correlate with cognitive outcome [34].

Long-term neurological and cognitive development of the IUGR infant at term have been studied extensively. The Ponderal Index among IUGR infants, but also among infants with a normal birth weight, is an independent predictor of neonatal morbidity: the lower the Ponderal Index the higher morbidity [25]. Learning difficulties, defects in speech and mild neurological deficits and behavioral problems have been reported to occur more in term neonates born SGA [35,36]. At school ages (7–8 years) temperamental differences and differences in play behavior are apparent [37], most probably contributing to increased rate of school failure found in IUGR infants.

Long-term morbidity might be resulting from subtle nutritional insults to the brain in utero. Although the brain growth spurt, being the most vulnerable period of the human brain, spans a broad period between mid pregnancy and 6 months of postnatal age [38,39], it is shown that growth failure occurring around term shows a strong association with cognitive disturbances as a poorer mental and psychomotor development at two years of age [40]. However, not all studies, even at preschool age show this trend of increased problems in growth restricted infants [41,42]. Besides neurodevelopmental consequences it is now also clear that children who were undernourished during pregnancy (e.g. born with a birth weight more than 2 SD below the mean birth weight) and especially in combination having had a compensatory growth trajectory during childhood have an increased risk in later life for diabetes, hypertension and cardiovascular diseases [43].

Given the data from studies concerning the effect of under-nutrition on the brain and the effects on long-term cognitive and behavioral outcome, evaluation of the possible clinical benefit of early induction of delivery, pre-empting a detrimental effect of chronic under nutrition on the fetal brain intervention, is important. By such an intervention it might be possible to start earlier with a more optimal feeding, compensating for the poor intra-uterine environment. Induction of labor is very often common practice in cases of suspected IUGR [44,45]. In the Netherlands at 33 up to 36 weeks of gestation, 63% of IUGR pregnancies were induced, whereas from 37 weeks onwards this percentage is 23%; more than double the percentage in non-IUGR pregnancies. In a Dutch obstetric cohort of 14.294 primigravid women with IUGR pregnancies, 29% of these pregnancies were induced [46]. In these pregnancies complicated by IUGR, induction of labour was associated with an increased risk of instrumental deliveries and emergency caesarean section, but no difference in neonatal outcome immediately after birth was found.

At present, there is no uniformity on the management of women with IUGR at term. Although there is no doubt that the intra-uterine growth retardated fetus should be considered as high risk, and should be monitored, there is no consensus on which diagnostic methods to evaluate fetal condition and subsequent intervention is best. It is unclear whether in this situation either induction of labour or expectant management is beneficial for the mother and her baby, since evidence on the subject is lacking.

For preterm pregnancies complicated by intra-uterine growth retardation, an international randomised clinical trial recently showed that expectant management had little benefit over early delivery with respect to short term neonatal outcome [47]. However, results of this trial cannot be extrapolated to the situation at term.

The lack of consensus on the subject in the Netherlands is demonstrated by the fact that in 2002 in women with a SGA child, labour was induced in 32% of these women, whereas labour started spontaneously in 56% of these women, the remaining 11% had an elective caesarean section. These data are based on actual birth weight, and the clinical situation is even more complicated by the fact that the antenatal diagnosis of a SGA child is often difficult to make and easily missed in clinical practice.

In view of this clinical dilemma, we propose a randomised clinical trial in which induction of labour is compared with expectant monitoring in women with a suspected IUGR child at term. We will compare maternal outcome, neonatal outcome and maternal quality of life, as well as costs. Moreover, we will collect, in both randomisation arms, data of the diagnostic tests used in fetal surveillance, i.e. fetal heart rate pattern, sonographic measurement of the amniotic fluid index and Doppler measurement of the umbilical artery and the fetal medial cerebral artery in women.

## Methods/design

### Aims

The aim of this study is to investigate whether induction of labour or expectant management is the best strategy in terms of neonatal and maternal morbidity and mortality, costs and maternal quality of life aspect in pregnancies complicated by IUGR from 36 weeks gestational weeks onwards.

### Study design and setting

We will perform a randomised controlled multi centre study.

This trial is embedded in the Dutch Obstetric Consortium, a collaboration of obstetric hospitals in the Netherlands. Approximately 40 hospitals, including all 10 university hospitals, teaching hospitals and district hospitals will participate in this trial.

### Participants/eligibility criteria

All women with a singleton pregnancy, with a child in cephalic presentation, with suspicion of IUGR (Fetal Abdominal Circumference < 10^th ^centile, Estimated Fetal Weight < 10^th ^percentile as defined by local protocols), or decreased relative growth though still > 10^th ^centile, e.a. from 70^th ^centile to 40^th ^centile) are eligible. Gestational age should be between 36+0 weeks and 41+0 weeks. Women with a history of caesarean section, serious congenital defects, ruptured membranes, renal diseases, diabetes mellitus, or positive HIV serology will be excluded.

### Procedures, recruitment, randomisation and collection of baseline data

All women with a singleton pregnancy who present at one of the participating clinics will be referred to an obstetrician or a specifically appointed research nurse/midwife for counselling. Eligible women receive participant information. After written consent, they are randomised by means of a web-based application. Stratification will be applied for previous vaginal birth (nullipara versus multipara) and for centre. Randomisation will be in a 1:1 ratio for induction of labour or expectant management.

Patients that withhold consent for randomisation are asked permission for data collection on pregnancy outcome. Participation to the quality of life study and long-term follow up (Child Behavioural Check Lists-CBCL and Ages and Stages Questionnaire-ASQ) is asked separately.

Baseline demographic, past obstetric and medical histories will be recorded for all women. Cervical length will be measured at the time of randomisation. The quality of life questionnaires are filled out before randomization, after randomization, 6 weeks postpartum and 6 months postpartum. The questionnaires contain the Hospital Anxiety and Depression Scale (HADS), EuroQoL 5D3L, Short Form (SF-36), Symptom Check List (SCL-90), and questions on background characteristics, intervention preparedness, risk perception and experience with the current pregnancy.

### Intervention

When randomised to the induction arm, induction of labor must start within 48 hours after randomisation. Induction of labor can be proceded according to local protocol (among other things cervical ripening with prostaglandin-gel or tablets or with amniotomy, with or without the use of oxytocin). When allocated to the expectant management group patients will not be induced unless the fetal or maternal condition deteriorates and this is for the attending obstetrician a reason for induction. The patients will be observed, e.g. with fetal and maternal monitoring according to local practice, until labour starts spontaneously. However, monitoring must at least include measurement of the umbilical artery Doppler waveform, fetal heart rate tracing, blood pressure and urine analysis for albuminuria weekly. Doppler studies of the medial cerebral artery are optional. Reasons for interventions and time interval between randomisation and labour will be collected.

### Follow up of women and infants

All details of delivery, maternal and fetal assessments and admittance during pregnancy are recorded in the case record form that is accessible at the website. In case of admittance of the child to the neonatal intensive care unit, details of this admittance are also recorded.

Long-term follow up of children will be done by recording growth after birth as measured at the local infant follow up clinics.

### Outcome measures

The primary outcome measure will be a bad composite neonatal outcome. Adverse neonatal outcome will be defined as death before hospital discharge, a 5-minute Apgar score < 7, an umbilical artery pH < 7.05 or admission to the neonatal intensive care. Secondary outcome measures are mode of delivery and time until delivery, length of admittance at the neonatal intensive care, maternal morbidity, hospitalisation of the mother for fetal and maternal surveillance, quality of life, and costs. In the present proposal, no funding is asked for long term follow-up of the child, yet. However, if additional funding can be obtained children's behavioural-, and neuro development will assessed by administering with a postal enquiry the Child Behaviour Checklist-CBCL and Ages and Stages Questionnaire- ASQ by their parents after 2 years.

### Statistical issues

#### Sample size calculations

The study is designed as an equivalence study, whereby both treatments will have the same incidence of the primary outcome measure of combined bad neonatal outcome. This incidence is assumed to be 6% [46]. The null hypothesis is that both treatments will not be equivalent. To detect equivalence with a power of 80% a sample size in both groups of 325 will be needed (PASS SOFTWARE). The margin of equivalence, given in terms of the difference, extends from -5.5 % to +5.5 %. The actual difference is 0 %. The calculations assume that two, one-sided Z tests are used. The significance level of the test is 0.05.

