#### Data analysis

Data will initially be analysed according to the intention to treat method. The main outcome variable, 'bad neonatal outcome', will be assessed by calculating rates in the two groups, relative risks and 95% confidence intervals as well as numbers needed to treat.

Time to delivery will be evaluated by Kaplan-Meier estimates, with account for differing durations of gestation at entry, and will be tested with the log rank test. The other secondary outcome measures will be approached similarly to the primary outcome measure. The analysis will be stratified for parity and centre.

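### The stated primary analysis (relative risk, 95% interval, NNT) does not carry out the equivalence test that 325 per arm was sized for

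*Protocol article*

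**What the plan says.** All the relevant text is in the Protocol article, under Statistical issues.

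**Sample size calculations.** The design is explicit: "The study is designed as an equivalence study". The assumed incidence of the composite neonatal outcome is 6% in both arms, with a true difference of zero. The margin is set on the absolute scale: "The margin of equivalence, given in terms of the difference, extends from -5.5 % to +5.5" percent. The test and level follow: "The calculations assume that two, one-sided Z tests are used. The significance level of the test is 0.05". The resulting size is given as: "To detect equivalence with a power of 80% a sample size in both groups of 325 will be needed".

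**Data analysis.** After naming intention to treat, this section says that the main outcome will be assessed through rates in each arm, "relative risks and 95% confidence intervals", and numbers needed to treat. It does not mention two one-sided tests, the ±5.5-point margin, a confidence interval for the risk difference, or a 90% level.

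**The concern.** Two adjacent subsections describe the primary comparison, and they differ in two respects.

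- **Scale.** The powered test is on the risk difference. The analysis names the relative risk.
- **Level.** Two one-sided tests at 5% correspond to a 90% interval. The only interval named is 95%.

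An analyst who followed the Data analysis section to the letter would produce a relative risk with a 95% interval and would still not have tested equivalence. To reach a conclusion, that analyst would have to supply a rule, and the two obvious candidates are a 90% or a 95% interval for the difference against ±5.5 points. They have different power and can give opposite answers on the same data. The Economic evaluation section also builds on the equivalence design, so the choice affects more than the primary outcome.

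**Working it through.** **Inputs** (all from Sample size calculations): incidence p = 0.06 in both arms; true difference 0; margin m = 0.055 on the risk difference; n = 325 per arm; two one-sided Z tests; level 0.05; target power 80%.

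**Step 1: reproduce the plan's own figure.**

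Standard error of the difference: SE = sqrt(2p(1−p)/n) = sqrt(2 × 0.06 × 0.94 / 325) = 0.01863. Ratio m/SE = 0.055 / 0.01863 = 2.952.

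Power with a true difference of zero: 2Φ(m/SE − z) − 1.

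With one-sided 0.05 per test, z = 1.645: 2Φ(2.952 − 1.645) − 1 = 2Φ(1.307) − 1 = 2 × 0.9045 − 1 = **0.809**.

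Size needed for 80%: n = 2p(1−p)(z + 1.2816)² / m² = 0.1128 × (1.645 + 1.2816)² / 0.003025 ≈ 319.4, so 320 per arm.

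The plan's 325 per arm and 80% are therefore reproduced. Exact binomial enumeration of the rule that the unpooled Wald 90% interval lies inside ±5.5 points also gives 80.9%.

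**Step 2: the same sample judged on a 95% interval for the difference.**

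This corresponds to one-sided 0.025 per test, z = 1.960: 2Φ(2.952 − 1.960) − 1 = 2Φ(0.992) − 1 = 2 × 0.8395 − 1 = **0.679** (exact enumeration 0.676).

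Size needed for 80%: 0.1128 × (1.960 + 1.2816)² / 0.003025 ≈ 391.8, so 392 per arm.

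| Decision rule, on the risk difference | Power at 325 per arm | n per arm for 80% |
|---|---|---|
| 90% interval within ±5.5 points | 80.9% | 320 |
| 95% interval within ±5.5 points | 67.9% | 392 |

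**Step 3: how often the two rules disagree.** Under the plan's assumptions, the 90% interval is inside the margin and the 95% interval is not in about 13% of trials (exact: 80.9% − 67.6% ≈ 13.4%, because the stricter rule is nested in the other).

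Example: 27/325 (8.31%) against 20/325 (6.15%). The difference is 2.15 points, with SE = sqrt(0.0831 × 0.9169/325 + 0.0615 × 0.9385/325) = 2.03 points.

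- 90% upper limit: 2.15 + 1.645 × 2.03 = 5.49 points, inside the margin.
- 95% upper limit: 2.15 + 1.960 × 2.03 = 6.13 points, outside it.

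The example was chosen close to the boundary. It shows that a reversal can occur; the 13% shows how often.

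**Step 4: why the relative-risk interval cannot stand in.** A margin in points becomes a ratio only once a reference rate is fixed. At the planned 6%, +5.5 points is a ratio of 11.5/6 = 1.92 and −5.5 points is 0.5/6 = 0.08. At an illustrative 10% (my assumption), the same margin is 15.5/10 = 1.55 and 4.5/10 = 0.45. The document gives no ratio margin and no conversion, so the interval it names has nothing to be compared with.

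**The case against.** The strongest reply is that nothing is miscalculated and nothing is expressly contradicted. The sample size section fixes the test, its sidedness, its level and the margin in advance. Two one-sided tests at 5% are an accepted convention, and reporting 95% intervals beside such a test is common. The Data analysis sentence can be read as a list of reported estimates with no decision rule in it. The natural joint reading is then two one-sided tests for the decision and 95% intervals for description. The operational detail could be left to a fuller protocol or analysis plan that is not shown.

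Most of this stands. There is no arithmetic error, and the joint reading is plausible.

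A reader might go further and infer that the trial is underpowered, with a true power of 68% instead of 80%. The article does not support that. It nowhere says that equivalence will be judged on a 95% interval, and it lists that interval with relative risks, not with the risk difference. The 68% belongs to a rule the reader would have to supply. Nor is it fair to say that the level is left open until the data are seen, since 0.05 with two one-sided tests is stated beforehand.

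The reply does not remove the mismatch. The article does say how the main outcome will be assessed, and what it names is on a different scale and at a different level from the test it was powered for. That is more than omitted detail. Reading the interval as belonging to the relative risk also leaves the named analysis unable to address the margin at all.

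**Conclusion.** The concern holds as a mismatch between design and stated analysis, not as a fault in the sample size. The 325 per arm is correct for two one-sided 5% tests on the risk difference, with about 81% power. Carrying out the Data analysis section as written would not perform that test.

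The possible loss is conditional. Power falls from about 81% to about 68% only if equivalence is decided on a 95% interval for the difference, so that the chance of missing true equivalence rises from about 19% to about 32%. These figures rest on the plan's own inputs (6% in both arms, zero true difference, ±5.5 points), the normal approximation with unpooled variance confirmed by exact enumeration, and all 325 women per arm being analysed. No allowance for loss was included.

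**What to change.** In Data analysis, add a sentence saying that equivalence on the primary outcome is decided by the 90% confidence interval for the risk difference (two one-sided tests at 5%) lying wholly within ±5.5 percentage points, and that relative risks, 95% confidence intervals and numbers needed to treat are reported for estimation only. This brings the analysis onto the scale and level of the sample size calculation. The stated 80% power stands and no patients are added.

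If the sponsor prefers to decide on a 95% interval for the difference, say so in Data analysis and restate the power at 325 per arm in Sample size calculations as about 68%. That costs no patients but gives up the 80% target; keeping 80% under that rule would take 392 per arm, 67 more in each. Either choice should be on record before outcome data by arm are seen.

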#### Data analysis

Data will initially be analysed according to the intention to treat method. The main outcome variable, 'bad neonatal outcome', will be assessed by calculating rates in the two groups, relative risks and 95% confidence intervals as well as numbers needed to treat.

Time to delivery will be evaluated by Kaplan-Meier estimates, with account for differing durations of gestation at entry, and will be tested with the log rank test. The other secondary outcome measures will be approached similarly to the primary outcome measure. The analysis will be stratified for parity and centre.

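### The trial is sized to show equivalence on the risk difference, but the stated primary analysis is a relative risk with a 95% interval and does not carry that test out

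*Protocol article*

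**What the plan says.** Under Sample size calculations the design is explicit: "The study is designed as an equivalence study, whereby both treatments will have the same incidence of the primary outcome measure". The hypothesis is framed accordingly: "The null hypothesis is that both treatments will not be equivalent". The scale and margin are fixed: "The margin of equivalence, given in terms of the difference, extends from -5.5 % to +5.5" per cent. The test family is named as a basis for the sizing: "The calculations assume that two, one-sided Z tests are used", at a significance level of 0.05, with 80% power and 325 women per arm. The Economic evaluation section repeats that the clinical study has an equivalence design.

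The next subsection, Data analysis, is the only text on how the primary outcome will be analysed. It says the outcome "will be assessed by calculating rates in the two groups, relative risks and 95% confidence intervals as well as numbers needed to treat", by intention to treat initially, with stratification for parity and centre. It mentions no margin, no one-sided tests, no interval for the risk difference and no rule for concluding equivalence.

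The Discussion paragraph of the abstract adds: "This trial will provide evidence for which strategy is superior", across neonatal and maternal outcomes, costs and quality of life.

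**The concern.** Two adjacent subsections commit to different things. One fixes a hypothesis, scale, margin and test. The other fixes a different effect measure and an interval level that belongs to a different test. This is more than detail left out of a condensed article, because the analysis paragraph makes a positive choice and that choice does not match the design.

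Three things are at stake.

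- **Scale.** A relative-risk interval cannot be compared with a risk-difference margin unless a control rate is also fixed.
- **Level.** Two one-sided tests at 0.05 correspond to a 90% interval for the difference. The only level the analysis paragraph names is 95%, and the choice between them can decide the result.
- **Interpretation.** Without an equivalence rule in the analysis, nothing stops a relative-risk interval that includes 1 from being reported as equivalence. That reading would not keep the 5% error rate the design set.

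**Working it through.** **Inputs (Sample size calculations).** p = 0.06 in both arms, margin m = 0.055, true difference 0, one-sided α = 0.05 for each test, power 80% (β = 0.20), n = 325 per arm.

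**1. Reproduce the sample size.** For two one-sided tests with true difference 0 and unpooled variance:

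n = 2p(1−p)(z₁₋α + z₁₋β/₂)² / m² = 0.1128 × (1.645 + 1.282)² / 0.003025 = 319.3, so 320 per arm.

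The article states 325, which is 1.5% higher, so the figure reproduces. With α = 0.025 per test (a 95% interval) the same formula gives 391.8, so 392. The stated size therefore corresponds to a 90% interval for the difference.

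**2. Power at 325 per arm, by interval level.** SE = √(0.1128/325) = 0.01863. Power = 2Φ(m/SE − z₁₋α) − 1, with m/SE = 2.952.

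| Interval for the difference | Normal approximation | Exact binomial | n per arm for 80% |
|---|---|---|---|
| 90% | 80.9% | 80.9% | 320 |
| 95% | 67.9% | 67.6% | 392 |

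**3. The margin on the relative-risk scale.** RR = (c + 0.055)/c for control rate c. At 6% it is 11.5/6 = 1.92; at 3%, 8.5/3 = 2.83; at 10%, 15.5/10 = 1.55. Only the 6% comes from the article; the other two are illustrative.

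**4. What a non-significant relative risk would let through.** Exact binomial enumeration, 325 per arm. The first result column is the probability that the 95% log-relative-risk interval includes 1. The second is the probability that the 90% Wald interval for the difference lies inside ±5.5 points.

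| True rates | RR interval includes 1 | Equivalence shown |
|---|---|---|
| 6% and 6% | 95.3% | 80.9% |
| 6% and 9% | 70.2% | 33.7% |
| 6% and 10% | 53.7% | 18.1% |
| 6% and 11.5% (on the margin) | 29.9% | 5.4% |

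The middle column is an error rate only if someone reads an interval that includes 1 as equivalence.

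**5. Illustrative data sets, 325 per arm.**

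- 29 against 20 events: RR interval 0.84 to 2.51 (includes 1). The 90% interval for the difference is −0.6 to +6.2 points, so equivalence is not shown.
- 14 against 5 events: RR interval 1.02 to 7.68 (excludes 1). Even the 95% interval for the difference, +0.19 to +5.35 points, is inside the margin.
- 27 against 20 events: the upper limit for the difference is 5.49 points at 90% (equivalent) and 6.13 at 95% (not equivalent).

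So the two analyses can disagree in either direction, and the interval level alone can change the conclusion.

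**The case against.** The best defence reads the two subsections together. They sit under one heading, Statistical issues, and the first already supplies the null, scale, margin, test family and level. The rates promised in Data analysis are enough to compute the difference, and the number needed to treat is its reciprocal. A reader might infer that the trial cannot answer its own null hypothesis. The article does not support that: the ingredients are there, and what is missing is their use in the stated analysis.

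A reader might also infer that the plan will treat a non-significant relative risk as equivalence. It does not say so. It sets no decision rule for the relative risk, and the 30% against 5% contrast measures a possible misreading rather than the error rate of the written plan.

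Nor does the abstract's word for the better strategy show a superiority analysis of the primary outcome. The sentence covers costs and quality of life as well, and an overall preference on those grounds is compatible with neonatal equivalence. The number needed to treat is undefined only at a difference of exactly 0, and as a descriptive addition it is a minor matter.

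Finally, a condensed article may leave the estimator and decision rule to an analysis plan that is not shown. That excuses silence. It does not excuse naming a different effect measure and an interval level that does not match the sizing. That conflict stands.

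**Conclusion.** The point holds as a mismatch between design and analysis on the primary outcome: the analysis as specified does not carry out the equivalence test for which the trial was sized. The consequence that needs no assumed misuse is the interval level: power is 80.9% with a 90% interval for the difference and 67.6% with a 95% interval. The larger contrasts (about 30% against 5% at 6% and 11.5%; about 70% against 34% at 6% and 9%) are conditional on reading a non-significant relative risk as equivalence.

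A reader might go on to infer that 325 per arm is wrong. It is not: the figure reproduces once 0.05 is taken as the level of each one-sided test. All figures assume a 6% rate in at least one arm, complete outcomes in 325 per arm, and an unstratified comparison; the planned stratification is not modelled.

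**What to change.** In Data analysis, name the risk difference (induction minus expectant management) as the primary estimate, stratified for parity and centre as the plan already states. Conclude equivalence only if its 90% confidence interval, corresponding to the two one-sided tests at 0.05, lies wholly within −5.5 to +5.5 percentage points. This keeps 325 per arm and the stated 80% power. If a 95% interval is to decide instead, say so and restate the power as about 68%, or plan about 392 per arm for 80%.

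Keep the relative risk with its 95% interval as a secondary description, and state that a non-significant relative risk is not evidence of equivalence.

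Minor: report the number needed to treat only where a difference is shown, and align the abstract's wording with the equivalence objective for the neonatal primary outcome.

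With the 90% rule the cost is a few sentences, with no extra patients or data.
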